## Exclusion criteria:

i) Pregnant women above 28 weeks attending ANC in the 16 selected health centres of Masindi and Kiryandongo will be excluded

(ii) All pregnant women in Masindi and Kiryandongo who will not have enrolled for Antenatal Care visits in the targeted health centres by the time the two trail arms will be conducted.

(iii) Pregnant women in Masindi and Kiryandongo districts who would have enrolled for ANC in the selected health centres but found to be bed ridden or mentally disturbed.

All pregnant women recruited in to the study will be requested to provide two or three possible phone contacts through which they can be reached. These telephone contacts will be utilised during the follow-up stage in case the women do not make return visits. All health workers providing ANC care at the primary care facility will receive training in counselling. A standard operating procedure for the educational intervention at the ANC clinic to pregnant women will be developed (see annex 7.13), these messages will be adapted to suit the individual context and incorporate findings from formative surveys.

During ANC visits, qualified staff will first provide the more technical care to pregnant women and record all details on the patients card; this information will further be utilised by the team comprising of HA and CHWs to provide the targeted educational intervention; the promotional team will also engage the pregnant women to discuss in to details recommended aspects of care during pregnancy and newborn care like diet, birth preparation, danger signs in pregnancy, the advantages of delivering in the health facility and birth plans, care for the newborn including hygiene, breastfeeding care for the cord and warmth for the newborn.

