# 4.4.4 Methodology

### 4.4.5 Study design

We will conduct a community trial involving two arms: a community intervention trial.

1. One arm receives the routine ANC care available in the health facilities (standard care); this normally involves the provision of technical ANC services (history taking, palpation, PMTCT), group health education sometimes, and appointment for the next visit; rarely providing targeted or individualised health education
2. A second arm will receive in addition a *promotional team* comprising of a staff with a promotional profile (in this case health assistant) and three other CHWs providing educational interventions to augment the technical ANC intervention provided by qualified staffs. Health workers and CHWs will have in their possession mobile cell-phones. The mobile phones will be used by health workers to call CHWs to make reminders about return ANC visits for prenatal women, due dates for institutional deliveries, as well as providing additional educational information to pregnant women through the CHWs and any other consultations the CHW may want to make with health workers.

*Study population:*

The population to be studied will be pregnant women in Masindi and Kiryandongo districts who enrol for antenatal care in the 16 selected health centres for the two trial arms, with each trial arm utilising 8 health centres

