### 4.4.7 Study variables

## Independent/factor:

(i) Routine ANC care available in the health facilities (standard care);

(ii) *Promotional team* giving additional education care to pregnant women with periodic mobile phone reminders.

*Dependent/outcome variables*

1. Timely return ANC visits (return within seven days of the scheduled appointment date)
2. Completion of the four recommended ANC visits
3. Institutional deliveries
4. Newborn care practices:
5. Provision of warmth to the newborn
6. Initiation of breastfeeding within one hour of birth
7. Care for the cord
8. Immunization for the newborn-Polio 0 & 1; BCG within the neonatal period

We will, at the end of the study, assess perceptions of individual women who have participated in this intervention towards the integrated package by administering the tool described by Howie and others ([Howie J, Heaney D et al. 1998](#_ENREF_42)) elaborated in annex 15 (the Patient-Enablement Initiative (PEI).

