## Annex 9: Sub study three Flow-diagram for educational intervention

**Arm 1**

Routine ANC & Newborn Services only

Absence of individualised prenatal health education; no CHW deployed; no mobile phones

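### As written, section 4.4.6 lets women in both arms be telephoned after a missed return visit and trains all ANC staff in counselling, which conflicts with the control definition and could dilute the contrast

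*Protocol*

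**What the plan says.** **Phone contacts (4.4.6, text after the exclusion criteria).** "All pregnant women recruited in to the study will be requested to provide two or three possible phone contacts through which they can be reached". The next sentence gives the use: "These telephone contacts will be utilised during the follow-up stage in case the women do not make return visits". The section covers all 16 selected health centres, and neither sentence mentions an arm.

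**Training (same paragraph).** "All health workers providing ANC care at the primary care facility will receive training in counselling". Again there is no arm restriction.

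**Control arm.** Section 4.4.5 describes it as the routine ANC already available, with individualised education given only rarely. Annex 9 is stricter for Arm 1: "Absence of individualised prenatal health education; no CHW deployed; no mobile phones".

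**Tested intervention.** In 4.4.5 the phone component is indirect: "The mobile phones will be used by health workers to call CHWs to make reminders about return ANC visits for prenatal women". Section 4.4.7 describes the intervention as a promotional team "giving additional education care to pregnant women with periodic mobile phone reminders".

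**Outcomes.** Timely return (within seven days of the appointment) and completion of four ANC visits are two of the primary outcomes (4.4.6, 4.4.7).

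**The concern.** In this protocol a return visit is an antenatal return: the operational definitions, 4.4.5 and 4.4.7 all use the term that way. The stated trigger for using a woman's phone number is therefore failure to return for ANC, which is itself a component of two primary outcomes. Nothing prevents that call from being made to a control woman while she is still pregnant, or from encouraging her to attend.

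Counselling belongs to the promotional side of ANC that the trial sets out to strengthen. The operational definitions group it with health education, and the conceptual framework assigns education and counselling services to community health workers (CHWs). Training control-centre staff in it would move control away from routine care.

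Both routes would be expected to bias the comparison towards no difference. The protocol tries to limit contamination by assigning health centres at opposite extremes of the districts (4.4.9, 5.1). Distance does not help when the study's own procedures carry the exposure. Nor could the dilution be described afterwards, because the protocol does not require calls to be recorded by arm.

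**Working it through.** **Step 1. Set the sections side by side.**

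| Item | 4.4.6 | 4.4.5 and Annex 9, control |
|---|---|---|
| Telephone contact | Numbers from all recruited women, used when return visits are not made | Annex 9: no mobile phones |
| Counselling | All ANC health workers at the facility trained | Individualised education rare (4.4.5) or absent (Annex 9) |

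Taken literally, these do not describe the same control arm.

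**Step 2. Which outcomes can a call change?**
- Completed four visits: any call during pregnancy that leads to attendance can change it.
- Timely return: a call within seven days of the appointment can change that visit. A later call cannot rescue it and matters only through its effect on later visits.
- Institutional delivery: only indirectly, through restored contact or better counselling.

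**Step 3. Reproduce the planned sample size.** Inputs from 4.4.8: D = 2.5, z-values 1.96 and 0.84, π0 = 0.235, π1 = 0.335, loss 10%.

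n = D(1.96 + 0.84)²[π0(1 − π0) + π1(1 − π1)]/(π1 − π0)²
= 2.5 × 7.84 × (0.179775 + 0.222775)/0.01 = 789.0 per arm (stated: 788).

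789.0 × 1.10 = 867.9 (stated: 868). Reproduction needs a minus sign in the denominator; the plus sign as printed gives about 24. The control rate is the existing district rate of 23.5%, with no allowance for any effect of calls or training in control centres.

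**Step 4. Illustrate dilution.** Hold the intervention arm at 33.5% and raise the control rate to c. The effective sample is 788/2.5 = 315.2 per arm.

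Power = Φ( (0.335 − c)/√{[c(1 − c) + 0.335 × 0.665]/315.2} − 1.96 )

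For c = 0.255: the variance sum is 0.189975 + 0.222775 = 0.41275, the standard error is √(0.41275/315.2) = 0.0362, and 0.08/0.0362 − 1.96 = 0.25, so power is about 60%. The n for 80% power is 2.5 × 7.84 × 0.41275/0.08² = 1,264.05, rounded up to 1,265.

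| Assumed rise in control rate | Power, 788 analysed per arm | n per arm for 80%, before loss |
|---|---|---|
| 0 points | 80% | 789 |
| 1 point | about 70% | 987 |
| 2 points | about 60% | 1,265 |
| 3 points | about 48% | 1,671 |
| 4 points | about 37% | 2,299 |
| 5 points | about 27% | 3,345 |

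The rises are assumptions. The protocol gives no effect size for calls or training.

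**The case against.** The best defence is that 4.4.6 is ambiguous rather than contradictory.

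- **Purpose of the call.** The text says the contacts are used in follow-up, which runs to four weeks after pregnancy ends. The first procedure in Annex 15 has staff follow up later to record place of delivery. Tracing women who have stopped attending, only to learn their outcomes, is a natural reading. This stands in part: caller, timing and message are not given. But the stated trigger is a missed return visit, and nothing limits the call to tracing.
- **Not the tested component.** The intervention's reminders go from health workers to CHWs on study phones (4.4.5; Annex 15, second procedure). Annex 9's exclusion of mobile phones can be read as the counterpart of those phones, not as a bar on holding a participant's number. This stands. A call to the woman's own contact is a related prompt, not the package.
- **Training.** The sentence leads into the description of the intervention's work, so it may mean intervention centres only. If both arms were trained, the contrast would be the team and reminders on top of a shared background. That is a coherent design, but it is not the routine-care comparison in 4.4.5.

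Two stronger readings are tempting. A reader might infer that control women will receive a version of the tested intervention. The documents show only that this is permitted, and only in attenuated form, without the CHW team or scheduled reminders. A reader might also use the region's 29.4% fourth-visit rate (section 4.1) to count how many control women would be called. That figure is population coverage of a fourth visit, not a missed-appointment rate, and cannot serve that purpose.

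**Conclusion.** The point holds as a conflict in wording with a plausible bias towards no difference. It does not establish that control women will receive the intervention. Followed literally, 4.4.6 allows prompting of control women on completed four visits and, depending on timing, on timely return. It also allows counselling training of control staff. Either departs from control as defined in 4.4.5 and Annex 9.

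The size of the bias cannot be derived from the protocol. The only scale available is the illustration: a 2-point rise in the control rate of institutional delivery takes power from 80% to about 60%, and a 5-point rise to about 27%. This takes the protocol's design effect of 2.5 at face value, keeps the intervention arm at 33.5%, and assumes the size of the rise. It concerns institutional delivery, the one outcome the protocol sizes, whereas the calls act most directly on the two visit outcomes.

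This is more than a missing detail, because it bears on what the control arm is. It should be settled before enrolment.

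**What to change.** 1. **Study calls.** State in 4.4.6 that calls to participants' own contacts are for outcome ascertainment only. They follow the same schedule in both arms, are timed around and after the end of pregnancy, are completed within the four-week follow-up window, and are never triggered by a missed ANC appointment. The schedule should not simply wait until four weeks after the expected delivery date: that falls at or beyond the end of follow-up, and well beyond it after an early birth or a loss.
2. **Reminders.** State that intervention reminders run only through the CHW phone system.
3. **Training.** State which centres' staff receive counselling training. Either limit it to intervention centres during the trial, or give it in both arms and redefine the control arm and the trial's question to match.
4. **Log.** Record by arm every study call made before delivery, with date and reason.
5. **Reconcile** 4.4.5, 4.4.6 and Annex 9 so that they describe one control arm.

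The cost is mainly wording, plus a simple call log. Some women will be traced later, so loss to follow-up may be slightly higher. Loss should be watched by arm, since intervention women may also be reachable through CHWs.

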## 4.2.8 Study variables

- Perceptions of health workers about comprehensive maternal and newborn care
  - Provision of technical ANC services for example taking and recording BP, weight, screening for HIV integrated with,
  - Provision of less technical and more promotional services mainly health education
- Perception of health workers about working with Community Health Workers
- Knowledge of health workers about pre-natal care
  - Dietary requirement for pregnant women
  - Danger signs during pregnancy
  - Birth preparation
- Knowledge of health workers about neo-natal care
  - Hygiene and cord care
  - Warmth for the newborn
  - Early initiation and exclusive breast feeding
  - Recognition of danger signs

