**10 months**

# 5.0 Ethical issues and considerations

Clearance will be obtained from the Institutional Review Board of MakSPH and the National Council of Science and Technology in Uganda. Authorisation to perform this research in the two districts will be obtained from both the national Ministry of Health and the district authorities and health managers. Details and benefits of this survey will be presented to the district authorities in a half-day seminar. Informed written consent will be obtained from the health workers and other participating community members (lactating women, TBAs, elderly care givers). Assent will be obtained from senior members of a household in case participants are less than 18 years. Confidentiality will be maintained personal identifications will be stored and only accessed by the study team.

Details of the study will be explained to all participants and they will be informed to feel free to participate or not in the study with no undesirable consequences to them.

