# Annex 15: SOPs: Standard Operating Procedure and intervention packages

### i) Standard operating procedure and intervention package for educational intervention during ANC

**(**[**Bhutta Z, Sajid S et al. 2011**](#_ENREF_10)**)**

When the pregnant women enter the clinic room

1. Identify pregnant women with all of the following conditions:
2. First visit of the current pregnancy,
3. Not more than 28 weeks of gestation
4. Administer the consent form
5. If she consents then open a file for her
6. Request for her ANC card
7. Enter all personal details available on the ANC card in to the file
8. Record any telephone contacts that you can use to access her in future

name, age, ethnicity, parity, LNMP, EDD, gestation age of the first visit, history of previous pregnancy outcome of the previous pregnancy (baby – alive or dead, mode of delivery), distance from the health facility, marital status, history of previous ANC attendance-Number of attendance, delivery (home, health facility, TBA etc).

Note the date for the next appointment, (all this information will be used to tailor the discussions)

-if she consistently attended all the expected milestones-then you find out what her motivation was to do so, and whether she plans to do the same for the current pregnancy;

- If not consistent-discuss the reasons for inconsistencies and help her to find a solution,

- diet during pregnancy-find out what foods are readily consumed and what she can easily afford, what foods could be prohibited during pregnancy (caution about antagonising cultures-you can find another acceptable alternative source of the food value) and discuss the importance for balances in diet, fruits, green vegetables, proteins and carbohydrates,

- Discuss work related activities-how much she does and who helps her with the routine household and garden chores.

- Discuss importance of ANC even when she has been attending consistently, the advantages of delivering in the health facility even when she has been delivering at the health facility,

- Birth preparation-clean clothes for the newborn (emphasis that clean does not mean new!-even old rages can be patched together washed clean, clean environment for the newborn,

- caring for the cord, dangers of applying substances to the cord,

- Pre-lacteal feeds-and its disadvantages-explain how breast milk eventually comes and the usefulness of colostrum.

- Discuss bathing of the new baby how soon and how to delay (delay up to 24 hours),

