- Immunisation of the child, polio 0, BCG etc.

- Recognition of a sick child-hot to touch, refusing to feed, crying unusually,

All these information should be derived from discussions with the pregnant woman-not as a set of instructions to be strictly followed-compromises should be made at every stage-all that is agreed upon should be detailed down in the file. The counsellor should moderate the discussions, if the pregnant woman has come with a partner or a caretaker; both of them should be involved in the discussions even if the care taker is not pregnant-if there is a caretaker present then this should be recorded and state the relationship between them.

Tick the areas that were discussed, mark with a cross what you did not discuss with her, note down important decisions that you have agreed upon with the participant-you will use this as a reference point in subsequent meetings and discussions

Ensure that the discussion does not exceed 30 minutes unless there is expressed interest from the participant to continue. And this expression should be noted down in the file.

For subsequent visits indicate appointment dates and actual revisit dates

Later on follow-up for delivery and record where she has delivered from

Assess for the different practices outlined annex 6 will be used to assess the following outcomes

Place of delivery, Cutting of the cord, care for the cord, initiation of breast feeding, provision of pre-lacteal feeds, in case of illness how it was recognised, what action was taken, how soon was the care seeking from onset of disease or when the decision was made that the child was unwell, what facility did she take the child, outcome, at the periphery of assessment the researcher will want to know whether the child is still alive just at one month.

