### ii) Standard Operating procedure for the use of mobile cell phones

1. Only voice messages will be deployed in this intervention
2. Phones will be programmed to connect between CHWs, HAs, Health workers on call at the primary care facility and the reference hospital
3. Only the health centre staff cell phones will directly connect to the hospital in case of emergency evacuation of a pregnant woman or newborn baby
4. Community Health workers living in the community will own the mobile phones
5. CHWs will dial the midwife or health staff on duty to make any enquiries regarding pregnancy or newborn care as and when the need may arise;
6. CHWs will receive health specific advice from the technical staff based at the health facility-(a specific health staff will be scheduled on-call in order to respond to such enquires from the CHWs)
7. Midwifes will dial CHWs in case of any specific prenatal woman who may need a closer follow-up for her pre-existing medical condition or who requires a closer follow-up given specific complication with the current pregnancy
8. Midwife will also call CHWs to make reminders for ANC return visits and due dates for delivery for pregnant women
9. Midwives or health worker on-call will dial the emergency hospital number in case of evacuation of prenatal or newborn baby or both

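### Protocol 4.4.6 and Annex 15 set no limit on the clinical information that community health workers may use, and bring any companion into the tailored discussion without the woman's permission

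*Protocol*

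**What the plan says.** In the intervention arm, the text after the exclusion criteria in 4.4.6 says that "qualified staff will first provide the more technical care to pregnant women and record all details on the patients card", and then that "this information will further be utilised by the team comprising of HA and CHWs to provide the targeted educational intervention".

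Annex 15 turns this into operating steps:
- **Part i, the file.** After consent, a file is opened, with the instruction "Enter all personal details available on the ANC card in to the file". A list of demographic and obstetric items follows, and the information is to shape the discussion.
- **Part i, the companion.** If the woman comes with a partner or caretaker, "both of them should be involved in the discussions even if the care taker is not pregnant".
- **Part ii, the phones.** "Community Health workers living in the community will own the mobile phones". Midwives are to call CHWs about a particular woman who needs closer follow-up because of an existing medical condition or a complication.
- **Part iii, the records.** The Health Assistant makes sure that CHWs enter and archive all details about the woman.

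On confidentiality, section 5.0 has one sentence: "Confidentiality will be maintained personal identifications will be stored and only accessed by the study team".

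**The concern.** Annex 15 is what staff will follow at the clinic. As written, it lets lay workers who live among the participants see, keep and be phoned about a woman's clinical information, and nothing is marked as withheld. Antenatal care here includes HIV services, so the most sensitive item a clinic holds may be in that flow.

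The companion rule is a second route. The discussion is built on the woman's own history: previous pregnancies and their outcome, place of delivery, and past antenatal attendance. A partner or caretaker may not know all of this, and the woman is not asked before that person joins.

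What is at stake is harm to a participant that cannot be undone once information is out. Annex 9 gives the control arm no CHWs and no phones, so the exposure falls on the intervention arm alone.

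**Working it through.** No formula applies. The check is to follow the information from the clinic card to each person who may receive it, and then to compare that path with the confidentiality sentence.

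1. **What goes on the card.** Per 4.4.6, all details of the technical care. No item is excepted.

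2. **Does technical care include HIV services?** Yes. In 4.4.5, routine care covers "provision of technical ANC services (history taking, palpation, PMTCT". Among the study variables of sub-study one, 4.2.8 gives as examples of technical services "taking and recording BP, weight, screening for HIV integrated with". Chapter one also names HIV screening as a technical antenatal service.

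3. **Is the HIV result stated to be on the card?** No. It is a reasonable inference from steps 1 and 2. The quote from 4.2.8 comes from a list about health workers' perceptions and does not describe card content in the trial.

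4. **What is copied to the file.** Annex 15 i) asks for all personal details on the card, then lists name, age, ethnicity, parity, dates and gestation, previous pregnancy, distance, marital status, and previous attendance and delivery. HIV, PMTCT and laboratory results are not listed. The printed discussion topics leave them out too.

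5. **Does that list limit the rest?** Not explicitly. It concerns the file. The sentence in 4.4.6 concerns everything recorded on the card, and Annex 15 iii) speaks of all details about the woman. Neither refers to the list.

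6. **The phone route.** Annex 15 ii) does not depend on the card at all. A midwife calls a CHW about an identified woman because of her medical condition, and nothing says how much may be told.

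7. **The companion.** Annex 15 i) says that the companion should be involved, if one has come. The woman's permission is not mentioned.

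8. **Against section 5.0.** The sentence restricts access to personal identifications to a study team that the protocol does not define.
   - If CHWs are outside that team, their use and archiving of identifiable records conflicts with it.
   - If CHWs are inside it, the sentence permits their access and sets them no stated duty of confidentiality.
   - A partner or caretaker is outside it on either reading.

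Both readings leave a gap, so the passages have to be reconciled whichever was meant.

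**The case against.** The strongest reply is that a reader might infer more than the text says. Four points of it stand.

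- **HIV disclosure.** A reader might conclude that the protocol sends HIV results to CHWs. It does not say so, and the Annex 15 list and topics leave HIV out.
- **Disclosure to the companion.** A reader might conclude that staff must reveal card entries to a partner. The verb is should, it applies only if someone has come along, and the content is meant to be drawn out in discussion with the woman. No step tells the counsellor to read out a result.
- **Contradiction with 5.0.** A reader might call this a plain contradiction. CHWs who keep study files under a Health Assistant could be counted as study team, so the text supports only an unresolved tension.
- **Consent.** The file is opened only after consent. The consent form for antenatal women (Annex 13 in the contents list) is not available here and may cover CHW access or companions.

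It is also fair to say that using individual findings is the purpose of the intervention. Section 3.1 names as the problem that examination findings are not interpreted and discussed with women, and the operational definitions base the education on each woman's own problems. Barring CHWs from all clinical information would remove part of the intervention.

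These points narrow the concern without removing it. The rules in 4.4.6 and in Annex 15 ii) and iii) still carry no limit, and the companion rule still lacks the woman's permission.

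**Conclusion.** The concern holds as a missing safeguard for participants in the intervention arm. Clinical information passes to CHWs living in the community without a stated limit, a companion joins by default, and the one confidentiality sentence settles neither. That HIV results are part of the flow is an inference, and what the consent form says is unknown.

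A reader might go on to infer a measurable bias in the attendance and delivery outcomes. The documents do not support one, because they give neither an HIV prevalence nor a rate of avoidance. Purely as an assumption, take 3% to 10% of the 868 intervention women: 868 × 0.03 = 26 and 868 × 0.10 = 87. If one third of them stayed away, that is 1.0% to 3.3% of the arm. Only women who would otherwise have delivered in a facility count as lost successes. At the planned 33.5%, the loss is 0.03/3 × 0.335 = 0.3 points to 0.10/3 × 0.335 = 1.1 points, against a planned difference of 10 points. Both inputs are invented for scale. Moreover, avoidance caused by the package would be part of its real effect; only unequal consent or enrolment between the arms would be bias. The case for change is participant protection and does not need these figures.

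**What to change.** Four short changes:

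1. **4.4.6 and Annex 15 i) and iii).** State that HIV/PMTCT results stay with the clinical staff, are not copied to the file held by CHWs, and are not used by CHWs. Keep other examination findings available for the discussion. Let the list already printed in Annex 15 i) define the personal details that are copied, including the name, which is needed for reminders.
2. **Annex 15 ii).** Apply the same limit to the midwives' calls to CHWs.
3. **Annex 15 i), companion.** Make participation by a partner or caretaker conditional on the woman's permission, asked in private.
4. **Section 5.0.** Say whether CHWs belong to the study team, and bind them to confidentiality. Check that the consent form says the same.

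The cost is a few sentences; arms, outcomes and sample size do not change. The one loss is that CHWs cannot tailor the discussion to HIV/PMTCT results, which the midwife handles.
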